## **2.4    *Duration of the study***

To achieve the largest planned sample size of 504 patients we plan patient accrual during two consecutive months. This assumption is based on five participating centers, 2.000 treated patients per year per center, and a participation rate of 30% resulting in 600 patients after 60 days of accrual. The participation rate of 30% is a conservatory estimate based on the previous study (53.3%) and based on the underestimating definition of participation rate (as mentioned in chapter 2.3).

In case the planned sample size will be achieved earlier, accrual will continue to complete two months of accrual in order to facilitate additional exploratory analyses. In case the planned sample size should not be achieved after two months, accrual will continue until the planned sample size will be achieved if feasible in a reasonable amount of time. All centers will report the number of included patients on a weekly basis to the study coordinators.

### **3 Ethical aspects and data protection**

#### **3.1 Ethical and legal issues**

We do not expect any ethical or legal issues in the context of this study due to the non-interventional, cross-sectional, and anonymous study design. Study participation is voluntary. Participation or non-participation will not influence a patients' care by any means. Patient insurance is not necessary for the purpose of this study as no intervention other than the questionnaire administration at a routine visit will be administered.

The Ethics Committee of the Medical Faculty of Christian-Albrecht-University of Kiel will be asked for approval of the study prior to enrolment of the first patient. Each participating center will apply for approval of the respective Ethics Committee prior to enrolment of the first patient at their site.

#### **3.2 Data protection and data handling**

We do not expect any issues concerning data protection as all data retrieved within the study is anonymous due to the large number of potentially eligible patients (approx. over 2.000 patients treated in each radiotherapy department per year). There will not be any form of pseudonymization. Therefore, it will not be possible to link data to an individual patient.

As described above, the questionnaire and a patient information sheet will be handed out to eligible patients. Therefore, informed consent is given if a patient returns the questionnaire in a sealed envelope to the hospital staff. At the end of the study, the pooled envelopes will be opened only by members of the local study team. The anonymous data arising from the questionnaires will be extracted into an Excel file in each participating center. The Excel file will be protected by a password given by the local study team. Participating centers will send the Excel file via mail to the study coordinators. The passwords will be transmitted via phone call. The data of all centers will be pooled and analyzed by the study coordinators.

Due to the anonymous character of data in this study, the EU General Data Protection Regulation/ *Datenschutz-Grundverordnung* (GDPR / *DSGVO*) does not apply per Recital 26 GDPR / *Erw.Gr. 26 DSGVO*.

## **4 Publication**

We seek publication of results of this study. A priori, each participating center is respected for co-authorship (1 co-author) if at least 50 patients have been recruited in the respective center. Additional co-authors may be respected per authorship guideline of the jDEGRO if feasible.

## 5 Secondary analysis of global quality of life in comparison to general population data

### 5.1 Outline

Every other patient with cancer has an evidence-based indication for radiotherapy (10). The cancer disease itself or its treatment may negatively impact a patient's health-related quality of life (HRQoL). To measure HRQoL, patient-reported outcome measures (PROMs) are commonly used, for example in the form of validated questionnaires (11). These questionnaires may either investigate symptoms, functioning, or global HRQoL or each of these. For example, the generic PROM of the European Organization for Research and Treatment of Cancer (EORTC), the cancer core QLQ-C30, is commonly used in oncology (12).

Research on quality of life has recently rightfully focused on cancer survivors long after completion of treatment (13). Hinz and colleagues, for example, surveyed cancer patients at least 6 months after treatment and did not find a difference in global quality of life as compared to the general population (14). Yet patients could be exposed to decreased global quality of life at the end of a specific treatment such as radiotherapy despite significant advances in treatment techniques. More specifically, we lack a good understanding of overall quality of life of cancer patients in representative cohorts across disease types at the end of radiotherapy. This understanding could help to raise awareness for global quality of life and might underline the need for intensified supportive measures and improvements in treatment techniques.

The study of this protocol recruited patients in a coherent cross-sectional timeframe and included 11 centers across Germany resulting in over 1,000 participating patients. These patients also rated their global quality of life based on the EORTC QLQ-C30 (question 29+30) along with general covariables. [name] and colleagues published general population normative data on the EORTC QLQ-C30 in 2019. The dataset includes responses from over 1,000 individuals in Germany and has important general covariables.

Therefore, the primary aim of this secondary analysis is to compare global quality of life of cancer patients at the end of radiotherapy with the general population.

### 5.2 Methods

This is a secondary analysis with pooled data from two studies. Data from cancer patients at the end of a course of radiotherapy will be used as collected for the primary study of this protocol. In total, 1075 patients were recruited of which 1052 responded to global quality of life. The general population cohort, including 1006 individuals in Germany, is based on [name] et al. (15).

#### 5.2.1 Outcomes and variables

The primary outcome of this analysis is global quality of life based on question 29 and question 30 of the EORTC QLQ-C30 in cancer patients at the end of radiotherapy as compared to data

form a general population. Global quality of life will be calculated as suggested in the scoring manual of the questionnaire.

Covariables include general patient/individual characteristics including sex, age, education level, employment status, relationship status, and financial difficulties based on question 28 of the EORTC QLQ-C30.

Following groups will be applied to account for differences in categories of covariables in the cohort of cancer patients and general population cohort:

| Covariable                 | Cancer patients                                 | General population                | Present analysis                                                                   |
|----------------------------|-------------------------------------------------|-----------------------------------|------------------------------------------------------------------------------------|
| Sex                 | Male                                            | Male                              | Male                                                                               |
|                            | Female                                          | Female                            | Female                                                                             |
| Age                 | continuous                                      | continuous                        | continuous                                                                         |
| Education           | None                                            | Less than compulsory              | Less than compulsory                                                               |
|                            | < 10 years of education („Hauptschulabschluss“) | Compulsory                        | < 10 years of education („Hauptschulabschluss“)                                    |
|                            | 10 years of education („Realschulabschluss“)    | Some post compulsory              | 10 years of education („Realschulabschluss“)                                       |
|                            | > 10 years of education („Abitur“)              | Post compulsory below university  | > 10 years of education („Abitur“)                                                 |
|                            |                                                 | University degree                 | > 10 years of education („Abitur“)                                                 |
|                            |                                                 | Postgraduate degree               | > 10 years of education („Abitur“)                                                 |
|                            |                                                 | prefer not to answer              | missing                                                                            |
| Employment status   | Employed                                        | Employed full-time                | Employed                                                                           |
|                            |                                                 | Employed part-time                | Employed                                                                           |
|                            | Unemployed                                      | Unemployed                        | Unemployed                                                                         |
|                            |                                                 | Student                           | Unemployed                                                                         |
|                            |                                                 | Homemaker                         | Unemployed                                                                         |
|                            | Retired                                         | Retired                           | Retired                                                                            |
|                            | Self-employed                                   | Self-employed                     | Self-employed                                                                      |
|                            |                                                 | Other                             | Variable transformed according to free text entries if feasible, otherwise missing |
|                            |                                                 | Prefer not to answer              | missing                                                                            |
| Relationship status | Official                                        |                                   | Employed                                                                           |
|                            | Lives alone                                     | Single                            | Lives alone                                                                        |
|                            |                                                 | Separated/divorced/widowed        | Lives alone                                                                        |
|                            | Lives with partner                              | Married or in steady relationship | Lives with partner                                                                 |
|                            |                                                 | Prefer not to answer              | missing                                                                            |

### 5.2.2 Statistical analysis plan

Cohort characteristics will be displayed by descriptive statistics.

To analyze potential differences in global quality of life in both cohorts (cancer patients vs. general population) an ANOVA test will be performed for univariable and an ANCOVA test

will be used for multivariable analysis controlling for general patient/individual characteristics. Covariables in the ANCOVA test will include age, sex, relationship status, employment status, and subjective financial burden based on question 28 of the EORTC QLQ-C30 questionnaire. These covariables were chosen because of their potential influence on global quality of life and because of availability in both data sets.

A minimally important difference of 7 points of global quality of life in cancer patients compared to the general population will be considered as clinically meaningful (16). This falls into the range of 5 – 10 points which is often used as threshold and may reflect a compromise within this range as the cohort for cancer patients will consist of various different disease types.

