# 1 Introduction

Cancer patients face increased costs due to the disease or its treatment. Costs may be direct in terms of increased expenditures or indirect in terms of loss of income. This objective financial burden may cause subjective financial distress which in turn may result in financial toxicity (1). Financial toxicity has been linked to suboptimal treatment outcomes and patient satisfaction (2,3). Although financial toxicity has been studied extensively in the US, it has also been described in health care systems with public funding such as in Germany (4).

Radiotherapy is a major component in the treatment of cancer as approximately one out of two cancer patients receives radiotherapy at least once during the disease trajectory (5). Patients treated with radiotherapy face specific circumstances due to their treatment. This includes local side effects which may require topical supportive care which is often not reimbursed or also long treatment courses of up to 7 weeks. In this light, radiotherapy may cause both, increased direct costs as well as loss of income which may lead to financial toxicity. Yet only small exploratory studies have investigated financial toxicity in cancer patients treated with radiotherapy ([name] et al. 2022, accepted, *Strahlenther Oncol.*). A better understanding of the prevalence and associated risk factors of financial toxicity is desirable to mitigate its potentially deleterious effect on treatment outcomes and patient satisfaction.

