### **2.3 Statistical analysis plan**

One primary research question is the confirmation of the overall rate of financial toxicity per subjective financial burden (question 28 EORTC QLQ-C30) as detected in a previous exploratory study ([name] et al. 2022, accepted, Strahlenther Oncol.). This study employed the same eligibility criteria. The questionnaire from this study was only slightly modified for the present study. Questions on outcomes or variables for the primary research questions were not modified. In the previous study, overall 31% of the patients reported subjective financial distress ([name] et al. 2022, accepted, Strahlenther Oncol.).

To confirm this overall prevalence of financial subjective distress, we determined a sample size of  $n = 329$  based on the expected prevalence of 31% and assuming a precision of the estimate of 5%. Accordingly, if the prevalence of subjective financial distress falls into the 95% binomial exact confidence interval of 26.04-36.31%, this primary research question will be regarded as confirmed. The subgrades of subjective financial distress were rated by patients as 21% “a little”, 6% “quite a bit”, and 4% “very much” in the previous study. Yet of note, we considered the endpoint to be binary (absence/presence of financial distress) to determine the necessary sample size for estimating the prevalence.

Another primary research question is the confirmation of risk factors of financial toxicity per subjective financial distress as shown in the previous study ([name] et al. 2022, accepted, Strahlenther Oncol.). Statistically significant risk factors included lower net household income (OR= 0.28;  $p = 0.01$ ), higher direct costs (OR= 2.78;  $p = 0.021$ ), and higher loss of income (OR= 2.48  $p = 0.025$ ) per multivariate ordinal regression. Active employment status (OR= 16.96;  $p = 0.067$ ) and lower health-related quality of life (OR= 0.51;  $p = 0.058$ ) were also associated with higher subjective financial distress per multivariate ordinal regression.

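### The only covariate-adjusted comparison of global quality of life conditions on financial distress (Q28), a plausible mediator, so it does not estimate the overall difference named as the aim

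*Protocol*

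**What the plan says.** Section 5.1 of the protocol gives the aim of the added analysis: "to compare global quality of life of cancer patients at the end of radiotherapy with the general population". Section 5.2.2 plans a univariable ANOVA of the two cohorts and one multivariable ANCOVA. On the latter it states: "Covariables in the ANCOVA test will include age, sex, relationship status, employment status, and subjective financial burden based on question 28". The reason given is: "These covariables were chosen because of their potential influence on global quality of life and because of availability in both data sets". Section 5.2.1 lists Q28 among the general characteristics, after sex, age, education and employment: "relationship status, and financial difficulties based on question 28 of the EORTC QLQ-C30". Section 5.2.2 then names 7 points as the clinically meaningful difference, without saying whether the ANOVA or the ANCOVA estimate is to be held against it.

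Elsewhere the protocol gives Q28 a different role. Section 1 opens with "Cancer patients face increased costs due to the disease or its treatment", says that this burden may produce subjective distress, and adds that "radiotherapy may cause both, increased direct costs as well as loss of income which may lead to financial toxicity". Section 2.2 adopts subjective financial distress, measured by Q28, as the surrogate for financial toxicity. In section 2.3 Q28 is the dependent variable of the ordinal regression.

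**The concern.** Age and sex are fixed before anyone joins the patient cohort. By the protocol's own account, Q28 at the end of radiotherapy is not: having cancer and receiving radiotherapy, which is what separates the cohorts, may raise it. If Q28 also goes with lower quality of life, it lies on a path from cohort to outcome, and holding it fixed removes that path from the estimate.

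The two stated selection criteria, influence on quality of life and availability in both data sets, do not screen for this. A mediator satisfies both. The question not asked is whether cohort membership itself affects the variable.

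At stake is what the adjusted result means. Read as the answer to section 5.1, it could understate how much worse patients fare. A difference just above 7 points could be reported as falling below it.

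**Working it through.** Section 5.2.2 states no expected difference, power or sample size, so there is no figure of the plan to reproduce. The check is the algebra of linear models.

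**Formula.** The change in the cohort difference on adding Q28 equals (difference between cohorts in mean Q28) x (slope of quality of life on Q28). Strictly, both terms are conditional on the other covariables, and the slope is the one within cohorts.

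**Inputs from the protocol**
- Grades of Q28 in patients of the previous study: 21%, 6% and 4%, together 31% (section 2.3).
- Respondents: 1052 patients and 1006 from the general population (section 5.2).
- Threshold: 7 points (section 5.2.2).

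**Assumptions, not in the protocol**
- Any Q28 difficulty in the general population: 5-20%, with 31% added as the case of no cohort difference, and the same mix of grades as in patients.
- Slope: quality of life lower by 0.1-0.4 points per Q28 point.
- SD of global quality of life: 20-25 for precision, 21 as residual SD in simulation.

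**Step 1, mean Q28 in patients (0-100 scale).** 0.21 x 33.3 + 0.06 x 66.7 + 0.04 x 100 = 7 + 4 + 4 = 15.0.

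**Step 2, points removed by adjustment.** The population mean is 15.0 x prevalence / 0.31.

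| Population prevalence | Population mean | Difference in means | Slope 0.1 | 0.2 | 0.3 | 0.4 |
|---|---|---|---|---|---|---|
| 5% | 2.42 | 12.58 | 1.26 | 2.52 | 3.77 | 5.03 |
| 10% | 4.84 | 10.16 | 1.02 | 2.03 | 3.05 | 4.06 |
| 15% | 7.26 | 7.74 | 0.77 | 1.55 | 2.32 | 3.10 |
| 20% | 9.68 | 5.32 | 0.53 | 1.06 | 1.60 | 2.13 |
| 31% | 15.00 | 0 | 0 | 0 | 0 | 0 |

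Over 5-20% prevalence the range is about 0.5 to 5.0 points. It is zero where the cohorts do not differ on Q28.

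**Step 3, against sampling error.** The 95% half-width is 1.96 x SD x sqrt(1/1006 + 1/1052), which gives 1.7 for SD 20 and 2.2 for SD 25. The upper part of the range exceeds this and the lower part does not.

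**Step 4, simulation with Q28 as mediator.** With an assumed total difference of -8, the model without Q28 returned -8.0 to -8.1. The model with Q28 returned:
- -6.1 (slope 0.2) and -5.1 (slope 0.3), with population prevalence one third of 31%;
- -6.5 (slope 0.2) and -5.7 (slope 0.3), with population prevalence half of 31%.

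**Step 5, when the reading against 7 points changes.** If adjustment removes r points, the adjusted estimate falls below 7 while the overall difference is above it only when the overall difference lies between 7 and 7 + r. That is 7 to about 7.5 at the lower end of the range, and 7 to about 12 at the upper end. The value of -8 in step 4 was chosen near the threshold.

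**Step 6, reverse influence.** Section 2.3 reports that active employment and lower health-related quality of life "were also associated with higher subjective financial distress per multivariate ordinal regression", the latter with OR 0.51 and p = 0.058. Section 2.2 measures that quality of life by questions 29 and 30, the items that form the outcome in section 5. If Q28 followed from quality of life (OR 0.51 taken per SD as an assumption, prevalence 31% versus 13%), a true -8 would appear as about -5.7 after adjustment. This is a what-if, since the protocol does not establish that direction.

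**The case against.** Four points on the other side carry weight.

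- **The ANOVA shows the difference without Q28.** True, but it adjusts for nothing. If the cohorts differ in age or sex, it cannot stand in for an adjusted comparison, and no model with age and sex but without Q28 is planned.
- **Q28 is not purely downstream.** Section 2.3 reports lower net household income as a significant factor for Q28 (OR 0.28, p = 0.01), and income is not among the covariables of section 5.2.1. Dropping Q28 may leave some pre-existing financial difference unadjusted. This stands, and is the reason to keep a second model with Q28 rather than discard it.
- **A difference net of finances may be wanted.** Section 5.1 mentions supportive measures and treatment techniques, for which that quantity has a use. But the aim as worded is the plain comparison, and section 5.2.2 does not label the adjusted result as anything narrower.
- **Employment status may also change with illness.** The same question can be asked of it. The present point does not rest on it.

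A reader might also infer more than the protocol supports. It does not hold that Q28 is a consequence of low quality of life. Section 2.3 reports an association from an exploratory study, and making Q28 the dependent variable of a cross-sectional regression is not a causal claim. Collider bias is therefore possible but not established. Section 1 likewise says only that the disease and radiotherapy may lead to financial toxicity.

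**Conclusion.** The point holds as one of mismatch between aim and model. The only covariate-adjusted estimate in section 5.2.2 is a difference not explained by financial distress, while section 5.1 asks for the overall difference. This rests on Q28 being at least partly a consequence of disease and treatment, which section 1 describes as possible and section 2.2 builds on.

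The direction is conditional. Adjustment shrinks the difference if patients report more distress than the general population and distress goes with lower quality of life. The size is not known: zero if Q28 does not differ between cohorts, and up to about 5 points under the assumed prevalences and slopes. The patient figures come from the previous study, not from the 1052 respondents analysed here.

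It would go too far to say that the comparison with 7 points is shown to be wrong. The protocol does not say which estimate is held against that threshold, and the reading changes only if the overall difference lies within a limited band above 7. The primary research questions on prevalence and risk factors are unaffected.

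**What to change.** In section 5.2.2:

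1. Make the main ANCOVA one without Q28, adjusting for age, sex, relationship status, employment status, and education, which section 5.2.1 already lists as a covariable and harmonises across the two data sets.
2. State that the cohort difference from this model is the one compared with 7 points.
3. Report the model with Q28 added as a sensitivity analysis, labelled as the difference not explained by financial distress.

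The cost is a few lines of wording and one extra model run, with no new data. The drawback is that some pre-existing financial difference may stay unadjusted in the main model. The sensitivity model shows how far the estimate moves when Q28 is held fixed, though it cannot separate pre-existing hardship from hardship brought on by the disease or its treatment.

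### Education is listed and harmonised as a covariable for the quality-of-life comparison but left out of the ANCOVA without a reason, so the adjusted cohort difference may stay confounded by it

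*Protocol*

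**What the plan says.** Section 5.2.1 (Outcomes and variables) sets out the covariables of the secondary analysis: "Covariables include general patient/individual characteristics including sex, age, education level, employment status, relationship status, and financial difficulties", the last taken from question 28 of the QLQ-C30. That makes six. The table that follows is introduced with "Following groups will be applied to account for differences in categories of covariables in the cohort of cancer patients and general population cohort". Its education rows map both cohorts to four common levels, with a refusal to answer set to missing.

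Section 5.2.2 (Statistical analysis plan) describes the ANCOVA as one that "will be used for multivariable analysis controlling for general patient/individual characteristics". It then gives the model: "Covariables in the ANCOVA test will include age, sex, relationship status, employment status, and subjective financial burden based on question 28" of the QLQ-C30. That makes five. The next sentence gives the basis for the choice: "These covariables were chosen because of their potential influence on global quality of life and because of availability in both data sets".

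Section 5.2.2 also sets the yardstick for interpretation: "A minimally important difference of 7 points of global quality of life in cancer patients compared to the general population" counts as clinically meaningful.

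**The concern.** Education is the only variable in the 5.2.1 list that does not reach the model, and no reason is given. It meets the availability criterion, because the table recodes it for both cohorts. On the other criterion, 5.2.1 gives it the same standing as the five variables that were kept.

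The comparison of cancer patients with the general population is the primary aim of section 5. It is not randomised, and the two cohorts come from separate studies. Regression adjustment is the only control of confounding that the section describes. If the education mix differs between the cohorts and education is related to global quality of life, the five-variable model attributes part of the education effect to cohort membership. With more than 2,000 respondents random error is small, so a systematic error of one or two points weighs more than it would in a small study.

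**Working it through.** **Comparison of the lists**

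| Covariable | Listed in 5.2.1 | In the ANCOVA, 5.2.2 |
|---|---|---|
| Sex | yes | yes |
| Age | yes | yes |
| Education level | yes, recoded to four levels | no |
| Employment status | yes | yes |
| Relationship status | yes | yes |
| Financial difficulties (question 28) | yes | yes |

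Six minus five leaves education as the only omission. Section 5 states no sample size, power or bias figure for this comparison, so there is no figure of the plan to reproduce.

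**Inputs for the scale**

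- From the protocol: 1052 cancer patients with a global quality-of-life response and 1006 general-population respondents (section 5.2); threshold of 7 points (section 5.2.2).
- Assumed, because the protocol gives none of them: SD of global quality of life 20 to 25 points; between-cohort difference in the share with higher education, given the other covariables, 0 to 30 percentage points; difference in quality of life between education levels, given the other covariables, 0 to 10 points.

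**Random error**

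SE = SD × √(1/1052 + 1/1006), and the 95% half-width is 1.96 × SE.

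- SD 20: SE 0.88, half-width 1.73
- SD 22: SE 0.97, half-width 1.90
- SD 25: SE 1.10, half-width 2.16

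In all three cases the power to detect a 7-point difference exceeds 99.9%.

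**Possible bias from leaving education out**

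Bias = difference in share × education effect. Percentages in brackets are of the 7-point threshold.

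| Difference in share | Effect 0 | Effect 3 | Effect 5 | Effect 10 |
|---|---|---|---|---|
| 0 | 0 | 0 | 0 | 0 |
| 0.10 | 0 | 0.3 (4%) | 0.5 (7%) | 1.0 (14%) |
| 0.20 | 0 | 0.6 (9%) | 1.0 (14%) | 2.0 (29%) |
| 0.30 | 0 | 0.9 (13%) | 1.5 (21%) | 3.0 (43%) |

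The range is 0 to 3.0 points. A bias of 1 to 3 points is about 1 to 3 standard errors.

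**Simulation check of the middle case**

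The inputs were a true cohort difference of −5.0, higher education in 30% of patients and 50% of the general population, an effect of 5 points, SD 22, the protocol's cohort sizes and 1,000 runs. The mean estimate was −6.07 without education and −5.07 with it. The gap of 1.00 agrees with 0.20 × 5 = 1.0. The simulation contains no other covariables.

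**The case against.** Several points on the other side deserve weight.

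*The two sections need not contradict each other.* The list in 5.2.1 serves the whole secondary analysis, and 5.2.2 also plans descriptive statistics of the cohorts, for which harmonised education is needed in any case. A model may use a subset of the listed covariables. This stands: the fault is an unexplained omission, not a strict contradiction. It does not remove the fault, because the stated criteria would admit education too.

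*The list may be open.* The wording "Covariables in the ANCOVA test will include age, sex, relationship status, employment status, and subjective financial burden" could be read as non-exhaustive. The following sentence, however, treats the list as the chosen set, so the five-variable model is the one that would be run.

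*The education categories may not be equivalent.* This is the most substantial point. Cancer patients are classified by school-leaving level, whereas the general population is classified by attainment up to postgraduate degree. "Post compulsory below university", for example, is placed in the same common level as the Abitur. Misclassification could then differ between the cohorts being compared, and adjustment could leave bias or add some. This would be a respectable reason to leave education out, but the protocol does not give it.

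*Other covariables may absorb part of the effect.* Employment status and question 28 may carry some of the influence of education. This stands, and it is one reason why the range starts at zero.

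A reader might also infer that the adjusted difference is in fact biased by education. The protocol does not support this. Bias needs both an imbalance in education and an education effect, each given the other covariables, and the protocol reports neither. Nor does it say how the general-population respondents were recruited, so no imbalance can be inferred from the sampling.

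**Conclusion.** The point holds as an unexplained omission from the main adjusted model of section 5. Education is listed, available and recoded for the pooled data, yet it is absent from the ANCOVA, and the stated selection criteria do not account for that.

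Confounding by education is possible but not shown. Under the assumptions above it amounts to 0 to 3 points, with 1 point in the middle case, and its direction is unknown. Even the upper end is less than half of the 7-point threshold. It could change the clinical reading of an estimate close to that threshold, but would not overturn a large difference. The omission itself rests on the text alone; the size rests wholly on assumed imbalances and effects.

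It would also go too far to say that the plan leaves the model open: 5.2.2 names a definite set of five. What is unclear is whether education was left out on purpose. The cancer cohort's response counts are already reported in section 5.2, so the reason for either choice should be written down.

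**What to change.** Add education level, in the harmonised categories of 5.2.1, to the ANCOVA in 5.2.2, and report the five-covariable model as a sensitivity analysis.

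If the investigators leave education out because the categories are not comparable between the cohorts, 5.2.2 should say so, and the model with education should be reported as the sensitivity analysis. Either way the two sections then agree, and readers can see how far the cohort difference depends on education.

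The cost is small:

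- One phrase in the protocol and one additional model in the report.
- Up to three degrees of freedom (four levels) among 1052 + 1006 = 2058 respondents.
- Respondents with missing education drop out of the model or have to be imputed.
- Equivalence of the education categories remains imperfect, so adjustment may not remove all confounding by education. This should be stated as a limitation.
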